#### 2.4.1. Analysis Population Sets

All analyses will be conducted on the Intention-To-Treat (ITT: all enrolled patients undergoing the neurorehabilitation procedure) and Per-Protocol (PP: all patients completing the study without major protocol deviations) populations. All measured variables and derived parameters will be individually listed and, if appropriate, tabulated by descriptive statistics.

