## 2. Materials and Methods

### 2.1. Design

We will conduct a randomized open, prospective two-arm controlled trial with blinded clinical evaluations on the effectiveness of hippotherapy (plus conventional neurorehabilitation) versus conventional neurorehabilitation alone. Due to the nature of the clinical trial, participants will know which treatment they will receive and investigators may also be aware of the treatment modality during the patient inclusion/randomization process. In this context, a double- or single-blind procedure is not entirely appropriate/possible. In order to mitigate the effect of factors that are not related to the treatment or intervention being tested, the patient’s functional abilities and emotional sphere will be assessed by two external actors, i.e., two physiatrists associated with the Centre Hospitalier Sud Francilien (see below). These physicians will conducted blinded face-to-face clinical assessments (they have no link with the investigation staff; they do not have access to the whole eCRF; they will also be blinded to previous assessments; and patients and their caregivers will be carefully advised not to disclose the treatment modality they are following). The study will occur at the Equiphoria Institute (La Canourgue, France: https://www.equiphoria.com/en/; accessed on 8 September 2021) for the hippotherapy program and at the Neurology Service of the Centre Hospitalier Sud Francilien (CHSF Corbeil-Essonnes; https://www.chsf.fr/nos-service/medecine/neurologie/; accessed on 8 September 2021) for the conventional neurorehabilitation. Randomization will be stratified by age (18–59 years, 60–74 years, and ≥75 years), stroke type (ischemic versus hemorrhagic), and degree of disability (Rankin scores 3 or 4) to ensure the groups’ homogeneity. The randomization and anonymization of the patient will be performed automatically by an algorithm in the eCRF following the completion of the patient’s initial data at inclusion. The clinical tests will be stored (eCRF) in a secure digital platform of the external subcontractor (CRO) for delayed treatment.

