#### 2.2.2. Inclusion and Exclusion Criteria

Inclusion criteria:Age ≥ 18 years old;Ischemic or hemorrhagic acute stroke;Inclusion > 3 and ≤ 12 months post-stroke,Rankin score ≥ 3 and ≤ 4 at inclusion,Written informed consent,Affiliation to social security,Hip minimal abduction of 25 degrees bilateral with no history of hip dislocation and/or dysplasia,Certificate of non-contraindication.

Exclusion criteria:Major cognitive impairment affecting comprehension (Mini Mental State Examination test < 24 points);Global or sensory aphasia;Neurological or psychiatric co-morbidity (other than mild to moderate post-stroke depression);Evidence of uncontrolled seizures;Substance abuse;History of uncontrolled pain;History of allergic reactions to dust and/or horsehair, or severe asthma;Body weight ≥ 110 kg;Contraindications to physical activity;Inability or medical contraindication to travel to the Institute Equiphoria;History of therapeutic horse riding or hippotherapy during the last 6 months;Pregnant or lactating women;Patients participating in other biomedical research or in a period of exclusion.

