#### 2.4.2. Statistical Analysis

Statistical methods will be in accordance with the CONSORT statement for reporting of randomized trials. Appropriate non-parametric statistics will be used to evaluate the comparability of the intervention and control group at baseline in terms of the clinical characteristics. If, despite the stratified randomization procedure, the groups are not comparable for one or more background variables, those variables will be routinely employed as covariates in the subsequent analyses. The scores for each variable (primary and secondary endpoints) will be calculated according to the published scoring algorithms. Intergroup (effect of the treatment on the measured variable, compared to the control) and intragroup (evolution of the measured variable on the same group) differences in the mean scores over time will be tested using a multilevel analysis. The effect sizes will be calculated using standard statistical procedures. All analyses will be conducted on an ITT basis. PP analyses will also be carried out (as secondary analyses). To test the effectiveness of hippotherapy intervention on functional independence (FIM; primary outcome), non-parametric ANOVA measures for non-linear scores (Friedman’s test for paired data) will be conducted. In addition, to test the effectiveness of the intervention on the secondary outcome variables, including the caregivers’ measurements, non-parametric ANOVA procedures (Friedman’s test for paired data) will also be applied. Post hoc analyses (e.g., additional correlation and covariance statistical procedures) will be conducted according to the obtained results. They will fine-tune the initial data analysis by taking into account potential confounding factors. Given the power of the study (80%), the post hoc results will be statistically robust and therefore reliable. The threshold of statistical significance will be *p* = 0.05. The statistical analyses will be implemented by the CRO using SAS^®^ software (version 9.4, SAS Institute, Cary, NC, USA).

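### The set labelled intention-to-treat is limited to patients who undergo the procedure, so it omits randomised patients who never start

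*Protocol article*

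**What the plan says.** The protocol article names two analysis sets in section 2.4.1. The ITT set is "all enrolled patients undergoing the neurorehabilitation procedure". The per-protocol set is "all patients completing the study without major protocol deviations". Section 2.4.2 then states "All analyses will be conducted on an ITT basis", with per-protocol analyses as secondary, and adds "Statistical methods will be in accordance with the CONSORT statement for reporting of randomized trials".

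Section 2.1 fixes the time of randomisation: it is "performed automatically by an algorithm in the eCRF following the completion of the" initial patient data at inclusion. The same section says the trial is open, in that "participants will know which treatment they will receive". It places hippotherapy at the Equiphoria Institute and conventional rehabilitation at the hospital where, under section 2.2.1, patients are recruited. Section 2.1.1 has the hippotherapy programme begin with a two-week daily cycle.

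**The concern.** Whether a patient undergoes the procedure is settled after randomisation. A set that depends on it is no longer the set that randomisation balanced. In an open trial, the decision to start can depend on the arm, on the patient's condition and on expectations about the allocated treatment.

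The primary FIM comparison could then be made between groups selected after allocation while being reported as ITT. The document offers no fallback analysis: nothing in it covers every randomised patient as allocated. With 52 patients planned, a few exclusions are a visible fraction of an arm.

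**Working it through.** **Step 1. Who falls outside the set.** This part is a reading of the text, not arithmetic. Three kinds of randomised patient can be set against the two definitions in section 2.4.1:

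| Randomised patient | ITT set as written | Per-protocol set |
|---|---|---|
| Starts and completes without major deviation | in | in |
| Starts, then stops or deviates | in | out |
| Starts no rehabilitation at all | out | out, if never starting counts as a major deviation |

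The third row is possible because randomisation (section 2.1) precedes treatment.

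**Step 2. How far the wording depends on the arm.** Neurorehabilitation procedure can be read in two ways.

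- Read as the allocated programme, a hippotherapy patient who refuses to ride is excluded even if he or she takes conventional care.
- Read as any neurorehabilitation, that patient stays in, and only those who start nothing are excluded, in either arm.

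The second reading lessens a possible imbalance. Neither reading gives all randomised patients.

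**Step 3. Hypothetical size.** The inputs are:

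- From the document (section 2.1.4): 52 recruited; target difference 22 FIM points; standard deviation 28.43.
- Implied: 52/2 = 26 per arm, as 22 per arm in the sample-size statement suggests equal allocation.
- Assumed, because the document gives no figure: k non-starters in one arm and none in the other, whose FIM change would be D points worse than that of the starters in that arm. The gap is set on the change scale because section 2.1.2 defines the endpoint as change.

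If the starters' mean change is m, the mean over all 26 is m − (k/26) × D. Dropping the non-starters therefore raises the arm mean by (k/26) × D.

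| k | D | Shift (FIM points) | Share of 22 |
|---|---|---|---|
| 3 | 10 | 3/26 × 10 = 1.2 | 5% |
| 3 | 20 | 3/26 × 20 = 2.3 | 10% |
| 5 | 10 | 5/26 × 10 = 1.9 | 9% |
| 5 | 20 | 5/26 × 20 = 3.8 | 17% |

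For scale, the standard error of a difference in means with 26 per arm and the planning standard deviation is 28.43 × √(2/26) = 7.9. The shifts run from 1.2/7.9 = 0.15 to 3.8/7.9 = 0.5 of a standard error.

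**The case against.** The strongest reply is that this is a loose parenthesis. The article states an ITT basis, ranks per-protocol second and invokes CONSORT, so the intent may be conventional and the full analysis plan may say so. That bears on how easily the text is repaired, but the article does not leave the definition open. It states one, and that one conflicts with its label.

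A reader might also infer that exclusions will fall mainly in the hippotherapy arm and so favour hippotherapy. The document does not support that, for these reasons:

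- It gives no non-start rate for either arm and nothing on the prognosis of non-starters.
- The procedure is not named as hippotherapy, and the treated arm also receives 18 weeks of conventional care.
- Foreseeable obstacles are screened. "Inability or medical contraindication to travel to the Institute Equiphoria" is an exclusion criterion, and section 2.2.2 requires a certificate of non-contraindication.
- The direction could be the reverse. Patients doing well might decline the travel, or controls might leave on learning that they will not ride.

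All of this stands. So does the point that a gap in FIM level would overstate the effect: the endpoint is change from baseline, and Rankin grade is a stratification factor. A 20-point gap in change is nearly the whole target difference, and so an extreme assumption.

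Finally, the remark that "investigators may also be aware of the treatment modality during the patient inclusion/randomization process" concerns blinding and concealment. It does not show that the analysis set is wrong.

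What the reply does not remove is that screening before randomisation cannot prevent refusal, fear or deterioration afterwards, and that the definition then drops the patient.

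**Conclusion.** The definition is wrong as written. It describes a treated (modified ITT) set, governs the primary analysis, and leaves no set that covers all randomised patients. This conclusion rests only on the wording of sections 2.1, 2.4.1 and 2.4.2.

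Bias is possible, because the trial is open and hippotherapy is delivered at a separate site, so non-starting may differ by arm. Its size and direction are unknown. The range of 1.2 to 3.8 FIM points holds only under the stated assumptions: 26 per arm, 3 to 5 non-starters all in one arm, and a change 10 to 20 points worse. It would be smaller with fewer non-starters, a smaller gap, or similar losses in both arms.

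**What to change.** Replace the definition in section 2.4.1 with: all randomised patients, analysed in the arm to which they were allocated, whether or not any session is attended. Collect FIM from non-starters who consent at the assessments already planned for weeks 22 and 48. If the present set is wanted, keep it as a sensitivity analysis under another name, such as treated set, and say whether any rehabilitation or only the allocated programme counts as undergoing the procedure. Eligibility needs no new rule here, since travel and the certificate are already selection criteria.

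The cost is one definition and the follow-up of a few patients at existing visits. The estimate may also be somewhat diluted. If starters gained the full 22 points over control and 3 of 26 non-starters gained nothing, the arm difference would be 22 × 23/26 = 19.5. With 5 non-starters it would be 22 × 21/26 = 17.8. That is the price of estimating the effect of allocation, and the sensitivity set can show the contrast.

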#### 2.4.2. Statistical Analysis

Statistical methods will be in accordance with the CONSORT statement for reporting of randomized trials. Appropriate non-parametric statistics will be used to evaluate the comparability of the intervention and control group at baseline in terms of the clinical characteristics. If, despite the stratified randomization procedure, the groups are not comparable for one or more background variables, those variables will be routinely employed as covariates in the subsequent analyses. The scores for each variable (primary and secondary endpoints) will be calculated according to the published scoring algorithms. Intergroup (effect of the treatment on the measured variable, compared to the control) and intragroup (evolution of the measured variable on the same group) differences in the mean scores over time will be tested using a multilevel analysis. The effect sizes will be calculated using standard statistical procedures. All analyses will be conducted on an ITT basis. PP analyses will also be carried out (as secondary analyses). To test the effectiveness of hippotherapy intervention on functional independence (FIM; primary outcome), non-parametric ANOVA measures for non-linear scores (Friedman’s test for paired data) will be conducted. In addition, to test the effectiveness of the intervention on the secondary outcome variables, including the caregivers’ measurements, non-parametric ANOVA procedures (Friedman’s test for paired data) will also be applied. Post hoc analyses (e.g., additional correlation and covariance statistical procedures) will be conducted according to the obtained results. They will fine-tune the initial data analysis by taking into account potential confounding factors. Given the power of the study (80%), the post hoc results will be statistically robust and therefore reliable. The threshold of statistical significance will be *p* = 0.05. The statistical analyses will be implemented by the CRO using SAS^®^ software (version 9.4, SAS Institute, Cary, NC, USA).

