#### 2.1.2. Primary Efficacy Endpoint

The Functional Independence Measure (FIM; lasting 30–45 min) (time frame: Changes from baseline to week 22; changes from week 22 to week 48) is an 18-item 7-point Likert scale evaluating physical, psychological, and social function, indicating the amount of assistance required for each task. A final total score is obtained ranging from 18 (complete dependence/total assistance) to 126 (complete independence) [37].

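### Covariates are chosen by whether the arms look different at baseline, so baseline FIM and the stratification factors are not fixed covariates and precision is lost

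*Protocol article*

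**What the plan says.** Section 2.4.2 (Statistical Analysis) begins with a between-arm baseline comparison: "Appropriate non-parametric statistics will be used to evaluate the comparability of the intervention and control group at baseline". If this shows that, despite stratification, "the groups are not comparable for one or more background variables, those variables will be routinely employed as covariates". No threshold for comparability is given.

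Section 2.1 (Design) names the stratification factors: "Randomization will be stratified by age (18–59 years, 60–74 years, and ≥75 years), stroke type (ischemic versus hemorrhagic), and degree of disability" (Rankin 3 or 4). No section puts them in the analysis unconditionally.

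Section 2.1.2 gives the time frame of the primary endpoint, FIM, as "Changes from baseline to week 22; changes from week 22 to week 48". Section 2.4.2 describes two analyses. For all endpoints, intergroup and intragroup "differences in the mean scores over time will be tested using a multilevel analysis". For FIM specifically, "non-parametric ANOVA measures for non-linear scores (Friedman’s test for paired data) will be conducted".

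The one covariate fixed regardless of imbalance is the record of rehabilitation sessions (Section 2.3.2). It is measured after randomisation, so it does not take the place of baseline adjustment.

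**The concern.** After randomisation, baseline differences between arms are due to chance. A test of them measures imbalance and says nothing about how strongly a variable predicts outcome. In a trial of 52 patients such a test misses sizeable imbalances in strong predictors and can flag variables that do not matter. Stratification makes age, stroke type and Rankin score the variables least likely to be flagged. Leaving prognostic stratification factors out of the model overstates the standard error.

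Two things are at stake. The adjusted model is settled only once the data are seen. And the trial gives up precision from variables it already needs for randomisation and for the endpoint.

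**Working it through.** **Inputs.** From Section 2.1.4: difference 22 FIM points, SD 28.43, two-sided 5%, two-sample t-test, 22 per arm analysed, 52 recruited (26 per arm). Assumed, because the article does not give them: the correlation ρ between baseline and week-22 FIM, equal SDs at both times, and a p<0.05 trigger for non-comparability.

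**1. The plan's own figure.** n per arm = 2 × (1.960 + 0.842)² × (28.43/22)² ≈ 26.2, so 27 (normal approximation) or 28 (t-test). The stated 22 per arm has 70.8% power by noncentral t. A one-sided 5% t-test at 22 per arm gives 81.1%. The stated 44 is therefore not reproduced as two-sided. That is a separate matter, but 70.8% is the unadjusted reference here.

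**2. Gain over the change score.** The comparator is change from baseline, since that is the endpoint.

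- If 28.43 is the score SD: change SD = 28.43 × √(2(1−ρ)); residual SD adjusted for baseline = 28.43 × √(1−ρ²). At ρ = 0.7 these are 22.02 and 20.30.
- If 28.43 is the change SD: adjusted SD = 28.43 × √((1+ρ)/2). At ρ = 0.7 this is 26.21.

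Power is from the noncentral t at 22 per arm, with one degree of freedom removed for the covariate:

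| ρ | Score SD: change → adjusted | Change SD: change → adjusted |
|---|---|---|
| 0.3 | 56.3% → 74.8% | 70.8% → 87.5% |
| 0.5 | 70.8% → 82.5% | 70.8% → 82.5% |
| 0.6 | 80.0% → 87.9% | 70.8% → 80.0% |
| 0.7 | 89.9% → 93.9% | 70.8% → 77.6% |
| 0.8 | 97.7% → 98.7% | 70.8% → 75.2% |
| 0.9 | about 100% for both | 70.8% → 72.9% |

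The strata add 2 + 1 + 1 = 4 degrees of freedom. This costs 0.3 points or less, before any gain from their prognostic value.

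**3. How the rule behaves.** A simulation used 40,000 replicates, 22 per arm and a Mann-Whitney p<0.05 trigger on baseline FIM. The trigger fired in about 5% of trials. For the change score with 28.43 as change SD, power unadjusted / under the rule / always adjusted was 71/71/81% at ρ = 0.5, 71/71/76% at 0.7 and 71/71/74% at 0.8. The always-adjusted values are about a point below the table because the formula ignores the variance cost of chance baseline imbalance. Type I error under the rule was 4.2%, 4.9% and 4.8% for change, and 4.5%, 3.7% and 3.3% if the raw score is analysed.

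**4. Imbalance left unadjusted.** Taking 28.43 as the baseline SD, with 26 per arm:

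- Standard error of the baseline gap = 28.43 × √(2/26) = 7.885.
- Gap needed for p<0.05 = 2.009 × 7.885 = 15.8 points.
- Median absolute gap = 0.6745 × 7.885 = 5.3 points.
- A gap g shifts the expected change difference by −(1−ρ) × g. At ρ = 0.7 that is 0.3 × 15.8 ≈ 4.7 points at the trigger, and 0.3 × 5.3 ≈ 1.6 points at the median, against the 22-point target.

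**The case against.** The strongest reply is that baseline FIM is already used. The endpoint is a change from baseline, and the multilevel analysis includes baseline as a time point. This stands: what is missing is a fixed baseline covariate, and the gain must be measured against the change score. Several stronger readings therefore fail.

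- A reader might infer that adjustment lifts power from 71% to 94% at ρ = 0.7. That compares adjustment with an unadjusted week-22 score, which is not the endpoint. Against change, the gain at ρ = 0.7 is 4.0 points (score SD) or 6.8 points (change SD).
- A reader might infer a bias of about 11 points (0.7 × 15.8). That is again a raw-score comparison, at a gap near the 95th percentile of chance imbalance.
- A reader might infer inflated type I error. The simulation shows it at or below nominal.
- A reader might infer that power is certainly short. If 28.43 is the score SD and ρ is 0.6 or more, the change score already reaches 80% at 22 per arm.
- A reader might infer that stratification guarantees balance. There are 3 × 2 × 2 = 12 strata for 52 patients, about four each, and no blocking method is described. Balance is likely but not assured.

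Time since stroke is neither stratified nor fixed as a covariate, and eligibility spans "Inclusion > 3 and ≤ 12 months post-stroke". That it predicts recovery in this trial is a judgement the article does not support with data.

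It cannot be said that the rule is merely a detail left to the analysis plan. It is stated explicitly, and no other section overrides it.

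**Conclusion.** The concern holds as a loss of precision and a data-dependent choice of model. For baseline FIM the rule behaves almost like no adjustment beyond the change score. Fixed adjustment gains power at every correlation examined up to 0.8, and up to 0.9 if 28.43 is the change SD: about 12 points at ρ = 0.5, and 4 to 7 points at 0.7. The direction is secure. The size is not, because the article gives neither ρ nor the meaning of 28.43. The gain from adjusting for the stratification factors cannot be quantified from the article. Undetected baseline imbalance could move the change difference by up to about 5 points at ρ = 0.7, and more typically by 1.6. These shifts assume a p<0.05 trigger and a baseline SD of 28.43.

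The rule also cannot operate in the test named for FIM, because Friedman's test takes no covariates. It can apply only to the multilevel analysis. This does not invalidate the trial, but it should be corrected before the data are analysed.

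**What to change.** 1. Remove baseline comparisons as a way of choosing covariates, and report baseline characteristics descriptively.
2. Name one between-arm model, multilevel or ANCOVA, as the primary FIM analysis in place of the Friedman test. A covariate list alone would leave the named primary test unchanged.
3. In every efficacy model, prespecify as fixed covariates the baseline value of that outcome, age, stroke type and baseline Rankin score. Where baseline is a covariate, it should not also be a response in the same model. Time since stroke may be added, if decided in advance.
4. State whether 28.43 is the SD of the score or of the change.

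The cost is a revision of the analysis text, including the primary method, and a few degrees of freedom (0.3 points of power or less for the strata). The baseline outcome values and stratification factors are already needed for the endpoints and the randomisation, so there is no new data collection.

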## 1. Introduction

Nearly 1.1 M Europeans suffer a stroke each year (17 M worldwide), which adds to 33 M stroke survivors [1]. Mortality is about 15% by 1 month, 25% by 1 year, and 50% by 5 years. A third of survivors experience disability (modified Rankin Scale scores 3–5) five years after having a stroke, due to physical, cognitive, and/or emotional deficits [2,3]. Much of the scientific efforts focus on medical programs involving acute care and inpatient rehabilitation. However, long-term disability often occurs and patients may continue to experience serious daily difficulties.

Outpatient neurorehabilitation programs are quite dissimilar, ranging from specialized interdisciplinary programs (involving different configurations of therapies) to limited individual therapies [4]. The need for better post-stroke care is still an issue. Indeed, the late rehabilitative phase is essential to both patients and their caregivers. Patients must receive a current continuum program instead of patchy modules of care shaped by a specific purpose with separate accountability [5]. Additionally, they need to understand the objectives of each phase of post-acute rehabilitation in different contexts and comprehend the challenges encountered at each level for the development of their empowerment and the appropriation of their future.

The notion of reaching a plateau in stroke recovery is questioned by a growing number of studies [6]. Accordingly, there is a need to design and assess therapeutic interventions in neurorehabilitation that promote sustained recovery from stroke over time [7,8]. Multidisciplinary programs need to be developed to cover the complex stroke continuum with the ultimate goal of reducing its large burden [7]. There is growing evidence that a multidisciplinary and cross-sectoral approach is pivotal to allow optimal post-stroke functional recovery [9,10].

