#### 2.1.3. Secondary Efficacy Endpoint

For the patient:

The modified Rankin Scale (mRS; lasting 5–15 min) (time frame: Changes from baseline to week 22; changes from week 22 to week 48) is a standardized measure that describes the extent of disability after stroke. The mRS is a single-item scale. It ranges from 0 (no symptoms) to 6 (death due to stroke) [38,39].

The Fugl-Meyer Assessment (FMA; lasting 30–35 min) (time frame: Changes from baseline to week 22) is a stroke-specific, performance-based impairment/recovery index. It is designed to assess motor functioning, balance, sensation, and joint functioning in stroke patients. Assessment items are scored based on the ability to complete the item using a 3-point Likert scale (0 = cannot accomplish; 1 = partially accomplished; and 2 = completely accomplished) where very severe ranges from 0–35, severe 36–55, moderate 56–79, and light > 79 (max. score 226) [40].

The Berg Balance Scale (BBS; lasting 10–15 min) (time frame: Changes from baseline to week 22) is a 14-item 4-point Likert scale where patients must maintain positions and complete moving tasks of varying difficulty. A global score is calculated out of 56, which represents the ability to independently complete the test [41,42].

The walking distance in 2 min (2-MWT; lasting less than 5 min) (time frame: Changes from baseline to week 22) reports the walking distance of the patient after 2 min. The number and duration of rests during the 2 min are also measured [43].

The Short-Form Health Survey (SF-36; lasting 10 min) (time frame: Changes from baseline to week 22; changes from week 22 to week 48) is a 36-item weighted Likert scale questionnaire, which measures quality of life (QoL) on 8 domains, both physically and emotionally based. The SF-36 is a generic patient-report measure used inter alia in stroke [44].

For the caregiver:

The Short-Form Health Survey (SF-36) for quality of life (time frame: Changes from baseline to week 22)—see above.

The Zarit Burden Inventory (ZBI; lasting 30 min) (time frame: Changes from baseline to week 22) is a 22-item 5-point Likert scale. The higher the score, the more extensive the burden. It is one of the most used instruments to assess caregiving burden in clinical and research settings [45,46].

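### The modified Rankin Scale, one ordinal item ending in death, has no ordinal between-arm analysis: the plan names only a mean-score comparison and a within-patient Friedman test

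*Protocol article*

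**What the plan says.** Section 2.1.3 lists the mRS first among the secondary endpoints, with change from baseline to week 22 and change from week 22 to week 48. It is a single item: "It ranges from 0 (no symptoms) to 6 (death due to stroke"). Section 2.2.2 restricts entry to "Rankin score ≥ 3 and ≤ 4 at inclusion".

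Section 2.4.2 sets the analysis. Its scope is general: "The scores for each variable (primary and secondary endpoints) will be calculated according to the published scoring algorithms". It then says that intergroup and intragroup "differences in the mean scores over time will be tested using a multilevel analysis", with no exception for the mRS. For effectiveness on the secondary outcomes it adds that "non-parametric ANOVA procedures (Friedman’s test for paired data) will also be applied".

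The article names no ordinal comparison of the arms. It does not say whether the multilevel model is linear, or how a patient who dies is entered.

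**The concern.** The mRS has seven ordered grades with no fixed distance between them, and the last is death. A difference in means treats every step as equal, including the step to death, so the reported effect is a fraction of a grade that depends on an arbitrary spacing.

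Friedman's test uses ranks, which seems to answer this, but it ranks repeated measurements within each patient. It detects change over time, not a difference between two independent groups. Neither named method is an ordinal comparison of the arms.

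At stake is the first-listed secondary endpoint, which is also one of three patient measures followed to week 48 (with the FIM and the SF-36). In a trial of 44 to 52 patients, a few extreme values can hide one-grade shifts.

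**Working it through.** **Plan's own figure.** None is given for the mRS. The only sample-size figure is for the FIM (section 2.1.4): 22 per arm, 52 recruited in total (26 per arm). It is used here only for arm size. Whether 22 per arm follows from its own inputs is a separate question.

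**1. What one death does to a mean, if scored 6.** Change from entry is 6 − 3 = +3 or 6 − 4 = +2. It offsets three or two patients who each improve by one grade, and fewer if they improve by more.
- Arm of 26: 3/26 = 0.115 or 2/26 = 0.077 grades.
- Arm of 22: 3/22 = 0.136 or 2/22 = 0.091 grades.

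**2. How many deaths.** The article gives no rate for eligible patients. The introduction gives a general one: "Mortality is about 15% by 1 month, 25% by 1 year, and 50% by 5 years".
- Hazard, 1 month to 1 year: ln(0.85/0.75)/(11/12) = 0.137 per year.
- Hazard, 1 to 5 years: ln(0.75/0.50)/4 = 0.101 per year.
- Risk = 1 − exp(−hazard × weeks/52): 4.2% to 5.6% over 22 weeks, 8.9% to 11.8% over 48 weeks.

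These figures describe stroke in general. Eligible patients are more than 3 months post-stroke, able to travel and cleared for the activity, so their mortality is likely lower. The range 0% to 15% per arm is therefore an assumption; 5% of 22 is about one death.

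**3. Power, mean score versus ordinal analysis.** Two-sided 5%, deaths scored 6 and equally frequent in both arms. Odds ratios (OR) and grade distributions are assumed.
- A: 26 per arm, OR 3, t-test on change v proportional odds with baseline mRS, 400 runs.
- B: 22 per arm, t-test v Wilcoxon test (standing in for an ordinal model), 3,000 runs. Control survivors in grades 1 to 5: 5%, 20%, 35%, 30%, 10%.
- C: 22 per arm, adjusted for baseline, analysis of covariance on scores v on ranks, 2,000 runs. Changes of −2, −1, 0, +1: control 3%, 22%, 65%, 10%; treated 12%, 50%, 35%, 3%.
- D: 22 per arm, OR 3, mean score v proportional odds, 300 runs.

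| Deaths per arm | A | B, OR 3 | B, OR 4 | C | D |
|---|---|---|---|---|---|
| 0% | 53 v 57 | 50 v 51 | 69 v 69 | 72 v 72 | 51 v 54 |
| 2% | – | – | – | – | 45 v 53 |
| 5% (A: 3–5%) | 40 v 51 | 35 v 40 | 51 v 60 | 45 v 57 | 31 v 41 |
| 10% (A: 6–10%) | 31 v 46 | 28 v 34 | 39 v 49 | 32 v 45 | 26 v 35 |
| 15% | – | 22 v 29 | 31 v 41 | 23 v 35 | – |

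Entries are power in percent. The smallest loss with deaths is about 2 points (B, OR 2: 18 v 20 at 5%). The largest is 46 − 31 = 15 points (A).

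A variant of A with 3% to 5% deaths in controls, where treatment also shifts deaths, gave 49 v 54 (OR 3) and 69 v 74 (OR 4), a loss of 5 points each.

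With no treatment effect, settings B to D gave false-positive rates near 5% for both approaches (D: 4% to 6% for the mean and 4% to 7.5% for proportional odds, 400 runs). The mean comparison is not invalid as a test.

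**4. Friedman's test.** Assumed: 44 patients, three visits, no arm difference, everyone tending to improve (changes of −1, 0, +1 with probabilities 30%, 62%, 8% and then 12%, 78%, 10%). It was significant in 67% of 2,000 runs. A significant result would say nothing about hippotherapy.

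**The case against.** The strongest reply is that the harm rests on an assumption the plan does not make. A reader might infer that the trial will score every death 6, so that one death cancels two or three recoveries. The article does not say so. Grade 6 is defined as death due to stroke only, assessments are face to face, and about 20% attrition is allowed for, so deaths might be treated as missing. A separate analysis plan, not shown, may settle this. The objection stands: the cancelling effect is conditional, and silence on deaths is not itself the fault.

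A reader might also infer that a mean comparison always loses power. It does not. Without deaths the gap is 0 to 4 points, and with 400 runs the simulation error on each estimate is about √(0.5 × 0.5/400) = 2.5 points.

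Nor does the plan ignore the ordinal nature of its scores, since it names a rank-based test. That test, however, cannot contrast the arms, so the gap remains.

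Finally, equal deaths combined with a shift among survivors break proportional odds, the assumption of the model proposed below. That is true of the tabulated scenarios. The variant in which treatment also shifts deaths gave a loss of 5 points, inside the range stated.

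**Conclusion.** The point holds in a limited form. Section 2.4.2 fixes a mean-score comparison for the mRS, and its other named method cannot compare the arms. The equal-spacing objection applies whether or not anyone dies. The power loss is about 0 to 4 points without deaths and very roughly 2 to 15 points with 2% to 15% deaths per arm. That range rests on assumed grade distributions, effect sizes and death rates, and on deaths being scored 6. Mortality in this selected population is not given and is likely below the general figures.

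The mRS is secondary and was not used to size the trial, so this does not affect the primary FIM conclusion. In the odds-ratio 3 scenarios neither approach exceeds 57% power. This is a cheap improvement, not a defect that endangers the trial.

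**What to change.** In section 2.4.2, or in the analysis plan if one exists:

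- Replace the mean-score and Friedman analyses of the mRS with a proportional-odds comparison of the arms at week 22 and at week 48. Include arm, baseline mRS and, where numbers allow, the other stratification factors (age band, stroke type).
- Report the common odds ratio with its 95% confidence interval, and the full mRS distribution by arm at each visit.
- State how deaths enter the analysis, including deaths not due to stroke.
- Align section 2.1.3, which defines the later endpoint as change from week 22 to week 48, with the week-48 comparison.

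The cost is a few lines of text and a standard SAS procedure. The downside is reliance on the proportional-odds assumption with about 44 to 52 patients; the displayed distributions let readers judge it. The stratification factors define 3 × 2 × 2 = 12 cells, or 44/12 = 3.7 to 52/12 = 4.3 patients per cell, so any extra factors should enter as main effects only.
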